#### Weaning protocol in the APRV Group

1) First Stage: Once the goal for oxygenation has been achieved, FiO_2_ is gradually reduced to ≤ 0.6, followed by a stepwise decrease in Phigh by 1–2 cmH_2_O to ≤ 26 cmH_2_O, unless the patient’s oxygenation deteriorates.2) Second Stage: After the improvement in the cause of respiratory failure, if pH ≥ 7.3, PaO_2_ > 70mmHg, SaO_2_ > 92%, FiO_2_ ≤ 40%, PaO_2_/FiO_2_ ≥ 200, Phigh is gradually and simultaneously reduced by 1–2 cmH_2_O and the release rate by 2 frequency twice daily unless the patient’s cardiopulmonary function deteriorates. Patients under deeper sedation (<-2) will have gradual and simultaneous reductions in analgesia and sedation based on the spontaneous minute ventilation target level and sedation goals combination.3) Third Stage: When patients achieve the criteria with Phigh ≤ 20 cmH_2_O and FiO_2_ ≤ 40%, they will undergo the daily SBT trial, similar to the weaning protocol in the LTV group.

### Tracheostomy

Patients will be considered for tracheostomy if they meet any of the following criteria: (a) The duration of mechanical ventilation exceeding 2 weeks; (b) Upper respiratory airway obstruction, such as laryngeal edema; (c) Impaired airway protection, such as swallowing disturbances, ineffective cough, and massive airway secretions [40].

### The summary of APRV and LTV protocols is presented in Table 1.

#### Data collection and confidentiality

An independent research assistant will initiate the collection of baseline information. Diagnostic data, clinical characteristics, physiological parameter examinations, laboratory findings, and details regarding the dosage and type of sedatives, muscle relaxants, opiates, and vasopressors, as well as adjuvant therapies and outcome measures will be collected. All personal information will be kept confidential for research purposes only. All study data will be collected anonymously and assigned an individual study number on all case report forms. These will be managed using a central web-based, password-protected, encrypted electronic case report form (eCRF) system. Paper versions of the eCRF will be used only in the event of system malfunction. Project data sets will be stored on the Project Accept website and robust password-protected access systems will be implemented to secure all local databases. Investigators will have direct access to their own site’s data sets and can request access to data from other sites. To ensure confidentiality, data dispersed to project team members will be stripped of any identifying participant information where the participants' identifying information will be substituted with an unrelated sequence of characters. Data entry will be guided and overseen by full-time scientific research personnel. Independent data management will oversee the trial during the trial period in accordance with the predefined Charter for the DMSC.

**Table 1 Tab1:** Summary of APRV and LTV protocols

	**APRV**	**LTV**
**Goals of mechanical ventilation**	PaO_2_: 55 -100 mmHg or SpO_2_: 92%-98%, PaCO_2_: 30-50 mmHg, and pH 7.30-7.45, and limit Pplat less than 30 cmH_2_O	
**Ventilator settings before randomization**	All patients initially A/C-VCV by ARDSnet, Vt was set at 6mL/kg/PBW initially, and PEEP was determined using the FiO_2_/PEEP table. Subsequently, the optimal PEEP was further adjusted based on oxygenation, compliance or P-V tool. Vt was adjusted to achieve goal of PaCO_2_ and pH.	
**Hemodynamic function management before randomization.**	Ensure sufficient cardiovascular system blood volume. For shock patients, rapid fluid resuscitation and, if necessary, combine with vasoactive drugs will be used to achieve MAP≥60 mmHg as soon as possible.	
**Ventilator settings after randomization**	**Phigh** was initially set at the Pplat measured at the previous VCV settings, not exceeding 30cmH_2_O.Then, Phigh was titrated to achieve the target PaO_2_and PaCO_2_.	**Tidal volume** (VT)was targeted at 6 mL/kg PBW. VT was adjusted within the range of 4–8 mL/kg PBW to achieve the goal of PaCO_2_ and pH, and target Pplat less than 30 cmH_2_O and driving pressure less than 14 cmH_2_O.
	**Plow** was 5 cmH_2_O, similar to physiological transpulmonary pressure	**PEEP** was adjusted based on the optimal oxygenation, compliance, or P-V tool.
	**Tlow** was initially set at 1.0~1.5 τ; then Tlow was adjusted according to the expiratory flow-time curve, ensuring that the end expiratory flow rate was ≥75% of the PEFR; If the Vt was < 6 ml/kg/PBW and patient-ventilator asynchrony occurred, Tlow was gradually extended, ensuring that the minimum end expiratory flow rate was at least > 50% of PEFR	/
	**Release frequency** was initially set at 10–14 frequency/min, or referenced to the original respiratory rate. Then release frequency was adjusted to achieve the goal of PaCO_2_ and PH, and the target spontaneous breath level. Thigh was only indirectly calculated based on Tlow and the release frequency	**Respiratory rate** was adjusted to achieve goal of PaCO_2_, PH (max 35 breaths per minute).
**Recruitment maneuver**	If the above interventions fail and patients without focal ARDS have been ventilated for less than 7 days, lung recruitment can be performed using the incremental PEEP approach.	
**Co-interventions**		
**Analgesia and sedation**	Analgesia goal: CPOT score of 0~2, Sedation: RASS score of -2 to 0. Nurses will continuously monitor the depth of sedation and adjust the dosages of analgesic and sedative drugs to maintain the target level of analgesia and sedation.	
**Jointly management of ventilator settings, analgesia, and sedation**	Clinicians will adjust APRV settings and the dosages of analgesic and sedative drugs to achieve the desired level of spontaneous minute ventilation, analgesia, and sedation.	Clinicians will titrate the ventilator settings and the administration of analgesic and sedative drugs to achieve the optimal patient-ventilator interaction and sedation goal.
**Adjuvant interventions**	In cases of persistent severe hypoxemia, if with no response to the assigned protocol and with a PaO_2_:FiO_2_ratio of <150mmHg for at least 12 hours, all adjuvant interventions can be utilized at the discretion of the clinician.	
**Prone positioning**	If there are no contraindications, prone positioning can be performed for more than 12 hours per day after careful preparation.	
**Neuromuscular blockade**	Neuromuscular blockade is indicated as the occurence of either of the following condition: a. If Pplat exceeds 30cmH2O, and spontaneous inspiratory efforts are clinically detected, b. Despite prioritizing optimization of ventilator settings, if patients exhibit rigorous respiratory effort, dyspnea, or breath stacking.	
**Inhalation of nitric oxide**	If patients do not respond to the above therapies and continue to experience severe hypoxemia with a PaO_2_/FiO_2_ratio<150 and an increase in pulmonary artery pressure, administration of 5-20 ppm iNO with concentration may be considered, with reassessment 48 hours later.	

#### Outcome

The primary outcome measure is mortality until day 28. Secondary outcome measures include physiological parameters at baseline, day 1, 3, and 7, encompassing ventilator settings and monitoring parameters, pulmonary mechanics such as plateau airway pressure, respiratory system compliance (Crs), and gas exchange parameters such as PaO_2_ and PaCO_2_. Additional variables include hemodynamic parameters, urine output, fluid balance, laboratory findings, and details regarding the dosage and type of sedatives and analgesics, vasopressors, lung recruitment maneuvers, and adjuvant therapies such as prone positioning, nitric oxide therapy, paralysis, and continuous renal replacement therapy. Outcome measures will encompass mechanical ventilation duration, ventilator-free days at day 28, ICU and hospital length of stay, rate of successful extubation, rate of tracheostomy, ICU and hospital mortality. Furthermore, any adverse events occurring during the study period, including barotrauma, ventilator-associated pneumonia, and other complications related to mechanical ventilation, will be collected and analyzed.

## An overview of the schedule of enrolment, interventions, and assessments is presented in Table 2.

### Sample size estimation and statistical analysis

#### Sample size

Based on previous research indicating a 37% mortality rate at ICU 28 days among moderate-severe ARDS patients receiving low tidal volume ventilation strategy [41], we postulated a 10% reduction in ICU 28-day mortality following the implementation of the early pathophysiology-directed APRV ventilation strategy compared to low tidal volume lung protective ventilation. Considering a hazard ratio of 0.66, a 90% power, and a two-sided significance level of 0.05, it is estimated that 762 patients are required to detect this difference. Accounting for approximately 10% loss in follow-up, enrollment of 840 patients (420 in each group) is necessary. An interim analysis will be conducted once 50% of the sample size is reached.

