#### Randomization and blinding

After enrollment, patients will be randomized in a 1:1 ratio to either the APRVplus group or the LTV group using a block randomization scheme. The random allocation list was crafted by a statistician uninvolved in the clinical aspects of the trial, utilizing a computer-generated random number list. Randomization will be stratified by enrollment site, pulmonary ARDS, and extrapulmonary ARDS. Assignment schedules were generated for each participating site, and allocation concealment was assured through a central web-based system (APRVplus.com) managed by Sichuan Zhikang Tech Co., Ltd. The treatment allocation for each patient will only be disclosed after their enrollment in the study.

As the intervention will be administered to critically ill patients on mechanical ventilation, most of whom are sedated, patient blinding is deemed unnecessary. Given that this is a nonpharmacological intervention, blinding the medical team is not feasible. Since there is no requirement for a committee to validate the study endpoint (death), outcome evaluators will not be blinded. However, the statisticians responsible for the analyses will be kept blinded to treatment groups for the duration of the study.

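### The hazard ratio of 0.66 does not match a 10-point fall from 37% mortality; for that fall, 762 patients give about 85% power, not 90%.

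*Protocol article*

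**What the plan says.** The Sample size section of the protocol article starts from "a 37% mortality rate at ICU 28 days among moderate-severe ARDS patients" under low tidal volume ventilation, taken from earlier research. It continues: "we postulated a 10% reduction in ICU 28-day mortality" with APRV. The design parameters and their result come in one sentence: "Considering a hazard ratio of 0.66, a 90% power, and a two-sided significance level of 0.05, it is estimated that 762 patients are required". The end of that sentence ties the number to the postulated reduction: "it is estimated that 762 patients are required to detect this difference". The recruitment target follows: "Accounting for approximately 10% loss in follow-up, enrollment of 840 patients (420 in each group) is necessary".

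The section does not say whether the 10% is absolute or relative, how 0.66 was obtained, or how many deaths are needed. The Statistics section analyses the primary outcome with Kaplan-Meier curves and a Cox model. The Randomization and blinding section sets 1:1 allocation.

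**The concern.** The closing words of the calculation attach the 90% power to the postulated mortality reduction, while the calculation runs on a hazard ratio. Once the control mortality at day 28 is fixed, the hazard ratio and the mortality in the other arm determine each other under the Cox model that the article plans to use. Only one of the two can be chosen freely, and the pair printed here does not agree.

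This is the design claim for the primary mortality endpoint. If it stands, a null result would be read as coming from a trial with a 10% chance of missing a 10-point benefit, when the chance is nearer 15%. A smaller question arises in the same paragraph: whether 840 really leaves 762 patients after 10% are lost.

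**Working it through.** **Inputs.** From the Sample size section: control mortality 0.37, a reduction of 10%, hazard ratio (HR) 0.66, power 0.90, two-sided alpha 0.05, 762 patients before loss, about 10% loss, 840 enrolled. From Randomization and blinding: 1:1 allocation. Inferred: APRV mortality 0.27, reading the 10% as absolute points.

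**1. Reproducing 762.** Schoenfeld's formula for 1:1 allocation is

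events = 4(z₀.₉₇₅ + z₀.₉₀)² / (ln HR)²

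With z-values 1.960 and 1.2816, (1.960 + 1.2816)² = 10.507, and ln 0.66 = −0.4155:

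events = 4 × 10.507 / 0.4155² = 243.4

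The mean event probability for 37% and 27% is (0.37 + 0.27)/2 = 0.32.

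N = 243.4 / 0.32 = 761, or 244 / 0.32 = 763 if events are rounded up first. The printed 762 lies between the two.

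Other routes do not reach it:

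| Method | N |
|---|---|
| HR 0.66 with the event rate that HR itself implies (Schoenfeld) | 769 to 772 |
| HR 0.66, Freedman events, divided by 0.32 | 785 |
| Two proportions, 37% vs 27%, 90% power | 910 to 912 |

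So 762 pairs HR 0.66 with an event rate built from 27%. This also supports the absolute reading of the 10%.

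**2. Do the inputs agree?** Under proportional hazards, survival at day 28 satisfies S(APRV) = S(control)^HR, whatever the shape of the baseline hazard.

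- From 37% and 27%: HR = ln(0.73)/ln(0.63) = (−0.3147)/(−0.4620) = 0.681.
- From 37% and HR 0.66: APRV mortality = 1 − 0.63^0.66 = 0.263, a reduction of 10.7 points.
- 0.66 is not another ratio for 37% vs 27% either: the risk ratio is 0.27/0.37 = 0.730 and the odds ratio is (0.27/0.73)/(0.37/0.63) = 0.630.

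**3. Power for 37% versus 27%.**

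power = Φ(√(events/4) × |ln HR| − 1.960), with |ln 0.681| = 0.384

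For 762 patients: events = 762 × 0.32 = 243.8; √(243.8/4) × 0.384 = 2.998; Φ(2.998 − 1.960) = 0.850.

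| Patients | Log-rank/Cox | Two proportions |
|---|---|---|
| 756 (840 less 10%) | 84.8% | 84.0% |
| 762 | 85.0% | 84.2% |
| 840 (no loss) | 88.3% | 87.6% |

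**4. What 90% would need.** Events = 4 × 10.507 / 0.384² = 285. N = 285/0.32 = 891 evaluable patients, 17% more than 762 (891/762 = 1.17). Rounding events up to 286 first gives 894.

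**5. The relative reading.** A 10% relative reduction gives 0.9 × 37% = 33.3%, so HR = ln(0.667)/ln(0.63) = 0.876. Power at 762 is then about 19%. This reading is much further from 0.66.

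**6. The loss allowance.** 762 × 1.1 = 838, which rounds to 840. Retaining 762 after a 10% loss needs 762/0.9 = 847. With 840 enrolled, 840 × 0.9 = 756 remain.

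**The case against.** The strongest reply is that 762 is correct for the parameter in its own sentence. At HR 0.66 it gives 90.0% power with a 32% event rate, or 89.7% with the event rate that HR implies. The mismatch is then only 0.7 points of APRV mortality (26.3% against 27%), and 27% is never printed. Rounding can absorb part of it: 36.5% control mortality with a 10.49-point reduction would print as 37%, 10% and 0.66.

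Most of that is true, and it locates the fault in the pairing of inputs, not in the events formula. It does not remove it. The text says 762 detects the postulated reduction, and at 10 points it does not do so with 90% power. Even the most favourable rounding gives only about 88.6%. The 27% is an inference, but the divisor of 0.32 supports it and the only other reading is far worse. A gap of 0.7 points looks trivial, yet it moves the required number from 762 to 891.

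It can also be said that 85% supposes a full 10% loss, and that censored patients contribute to a Cox analysis until they are lost. That stands: the fair range is about 85% to 88%. All of it is below 90%.

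On the loss allowance, (840 − 762)/840 = 9.3%, and the article says only approximately 10%. The slip is worth 0.2 points of power and is a side issue.

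Finally, the planning rate is itself uncertain, since the Introduction cites 40–50% mortality. At HR 0.681, power at 762 would be about 88% at 40% control mortality and 94% at 50%. If the 10-point difference is held instead, it falls to about 83% and 81%. This uncertainty is a reason to state clearly which effect is assumed; it does not reconcile the printed figures.

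**Conclusion.** The concern holds. The stated hazard ratio and the stated mortality reduction describe different effects, and the 90% power belongs to the larger of the two. For 37% versus 27%, power is about 85% with 756 to 762 evaluable patients (84% by a two-proportion test) and at most 88.3% if all 840 are followed. The type II error is therefore about 15% instead of 10% at the planned loss.

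This rests on the 10% being absolute points, on proportional hazards to day 28, on 37% control mortality and on 1:1 allocation. The number 762 is not wrong for a hazard ratio of 0.66. What is wrong is the claim that it gives 90% power for a 10-point reduction.

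**What to change.** Keep 840 and restate the sample size paragraph in one of two consistent forms:

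- 37% versus 27% mortality (hazard ratio 0.68), about 85% power with 756 to 762 evaluable patients; or
- hazard ratio 0.66, meaning 37% versus 26.3% mortality (10.7 points absolute), about 90% power.

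In either form, say that the reduction is in absolute percentage points, give the number of deaths the calculation rests on, and correct the loss statement: 840 with 10% loss leaves 756.

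The cost is wording only, with no extra patients and no change to the analysis. Under the first form the stated power falls by about 5 points. Under the second it stays near 90%, but the trial must own a slightly larger assumed effect. The Trial update section says recruitment was still ongoing when the article appeared. If results are reported before the correction is made, the report should give the power for the effect it names.

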**Table 2 Tab2:**
[figure not shown]
Overview of the schedule of enrolment, interventions and assessments

*APRV* airway pressure release ventilation, *LTV* low tital ventilation

#### Statistics

Continuous variables will be presented as mean and standard deviation, or median and interquartile ranges (IQR). Categorical data will be described with counts and percentages. Continuous variables with a normal distribution will be analyzed using the Student’s t-test, while those with a non-normal distribution will be compared using the Kruskal–Wallis analysis of variance. Dichotomous or nominal categorical variables will be analyzed using either the Pearson Chi-square or Fisher’s exact test. The trend over time in oxygenation and respiratory mechanics will be compared between the LTV group and APRV group using repeated-measures analysis. A two-sided *P* value of < 0.05 is considered statistically significant.

All analyses will adhere to the intention-to-treat principle (per protocol analysis). The primary outcome will be assessed using Kaplan-Meier curves and the ratio will be calculated with a 95% confidence interval using the Cox proportional hazard model. We plan to conduct a sensitivity analysis for the primary outcome using multiple imputation techniques only if follow-up data of 1% or more of the patients is lost. Interim analyses will be performed after recruiting half of the planned sample size to evaluate effects on clinical outcomes. The data monitoring committee would consider stopping the trial if there was evidence of harm with a one-sided *P* value < 0.01.

We will estimate the effects of the intervention using generalized linear models employing gamma distributions for lengths of ICU and hospital stay) or a truncated Poisson distribution (ventilator-free days). The treatment effect on 28-day mortality will be in subgroups based on PaO_2_:FIO_2_ (≤ 100 vs. > 100 mmHg) and pulmonary vs. extrapulmonary ARDS.

All analyses will be performed using the R software and subgroups will be evaluated using the chi-square test for homogeneity, we will employ the statistical software R Project Version 4.1.3 for Windows to carry out the analyses.

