#### Study population

The study will enroll adult patients aged 18 years and older who have been admitted to the intensive care unit (ICU) with moderate to severe ARDS, have undergone tracheal intubation, and received invasive mechanical ventilation for less than 72 h. The Berlin Conference definition will be utilized to identify patients with moderate-to-severe ARDS, including (A) hypoxemic respiratory failure with a PaO_2_/FiO_2_ ratio < 200 mmHg, (B) bilateral alveolar infiltrates on chest X-ray not present for more than 7 days, (C) respiratory failure not fully explained by cardiac failure or fluid overload, and (D) intubation on controlled ventilation and receiving PEEP ≥ 5 cmH_2_O [29].

Patients will be excluded from the trial if they meet any of the following criteria: (a) age over 85 years, (b) pregnancy, (c) suspected vasculitic pulmonary hemorrhage, (d) neuromuscular disorders known to prolong the need for mechanical ventilation, (e) severe chronic obstructive pulmonary disease, (f) severe hemodynamic instability (mean arterial pressure less than 60 mmHg despite sufficient fluid administration and use of high-dose vasoactive drugs (equivalent vasoactive drug dose: norepinephrine > 1.0 µg/kg/min)), (g) intracranial hypertension, (h) acute coronary syndrome, (i) pneumothorax, subcutaneous emphysema, pneumomediastinum, or pneumatocele, (j) patients in a moribund state or receiving palliative care only, (k) consent not obtainable, or (l) patients previously enrolled in another study.

Patients will be recruited from roughly 35 clinical sites in Mainland China with expertise in the identification and treatment of ARDS. Research investigators will provide training to the sub-research group at each sub-center on research protocols and implementation procedures. Coordinators at each participating site will assess potential candidates for enrollment. Once a patient is eligible for the study, a research investigator will obtain informed consent from the surrogate decision-maker. Subsequently, eligible patients will be enrolled and randomized, and initial ventilator adjustments will be made within 6 h.

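### The primary Cox model names neither the randomisation strata nor any baseline prognostic covariate; stating an adjusted model in advance is a free, modest improvement

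*Protocol article*

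**What the plan says.** Under Randomization and blinding, the protocol article states that "patients will be randomized in a 1:1 ratio to either the APRVplus group or the LTV group using a block randomization scheme", and then "Randomization will be stratified by enrollment site, pulmonary ARDS, and extrapulmonary ARDS". Under Study population, "Patients will be recruited from roughly 35 clinical sites in Mainland China".

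Under Statistics, the primary outcome is assessed with Kaplan-Meier curves, and "the ratio will be calculated with a 95% confidence interval using the Cox proportional hazard model". No stratum or covariate is attached to that sentence, and the model is not called unadjusted either. The same section uses ARDS type (pulmonary or extrapulmonary) and PaO2/FiO2 (split at 100 mmHg) only to define subgroups for 28-day mortality.

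Under Sample size, the inputs are a "37% mortality rate at ICU 28 days among moderate-severe ARDS patients receiving low tidal volume ventilation strategy"; "we postulated a 10% reduction in ICU 28-day mortality"; and "Considering a hazard ratio of 0.66, a 90% power, and a two-sided significance level of 0.05". From these, "it is estimated that 762 patients are required to detect this difference".

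**The concern.** Stratified randomisation forces the arms to be balanced on site and ARDS type. If those factors predict death, a Cox model that ignores them has a standard error slightly too large for the design, and its test rejects slightly too seldom. A model that also leaves out strong baseline predictors forgoes power that a pre-specified adjusted model would give.

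Two obvious predictors are already at hand. Age and PaO2/FiO2 are both eligibility criteria under Study population, so both are known for every patient at baseline. The plan itself treats PaO2/FiO2 and ARDS type as relevant to 28-day mortality, since it defines subgroups by them.

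At stake are a few points of power for the primary comparison and an interval that matches the randomisation. The validity of the trial is not at stake.

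**Working it through.** **1. Reproduce the plan's sample size.** Inputs from Sample size: HR 0.66, two-sided alpha 0.05, power 90%, mortality 37% and 37 - 10 = 27%.

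- Events (Schoenfeld) = 4 × (1.960 + 1.282)² / (ln 0.66)² = 4 × 10.51 / 0.1727 = 243.4, rounded up to 244.
- Mean event proportion = (0.37 + 0.27) / 2 = 0.32.
- Patients = 244 / 0.32 = 762.5, against 762 stated.

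The figure is reproduced with no covariate adjustment.

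**2. Count the strata.** 35 sites × 2 ARDS types = 70 cells. That is 762 / 70 = about 11 patients and 244 / 70 = about 3.5 deaths per cell on average.

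**3. Simulate the effect of adjustment.** N = 762, 35 sites of unequal size, 37% vs 27% mortality at 28 days, and 1,500 trials per scenario. The following are assumptions because the article does not give them: blocks of 4 within site × ARDS type, a 30/70 split of ARDS type, exponential death times, and all prognostic strengths. Baseline severity is one standardised covariate standing in for PaO2/FiO2 and age together.

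| | None | Moderate | Fairly strong | Strong |
|---|---|---|---|---|
| Site SD (log hazard) | 0 | 0.2 | 0.4 | 0.6 |
| ARDS type (log HR) | 0 | 0.2 | 0.4 | 0.4 |
| Severity (log HR per SD) | 0 | 0.4 | 0.7 | 1.0 |
| Power, no covariates | 85.1% | 83.9% | 85.2% | 86.3% |
| Power, ARDS type | 84.8% | 84.3% | 85.9% | 86.2% |
| Power, stratified by site, plus type | 84.1% | 84.0% | 86.5% | 87.1% |
| Power, stratified on 70 cells | 84.0% | 82.9% | 86.2% | 86.1% |
| Power, type + severity | 84.8% | 86.5% | 90.0% | 94.1% |

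Differences from the model with no covariates, in points:

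- stratified by site, plus type: -1.0, +0.1, +1.3, +0.8;
- stratified on 70 cells: -1.1, -1.0, +1.0, -0.2;
- type + severity: -0.3, +2.6, +4.8, +7.8.

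Monte Carlo error on one power figure is √(0.85 × 0.15 / 1500) = 0.9 point.

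The runs start near 85% rather than 90% because 37% vs 27% implies HR = ln 0.73 / ln 0.63 = 0.681 under proportional hazards, not 0.66. Power is then Φ(√244 × 0.384 / 2 - 1.96) = Φ(1.04) = 85%. That is a separate sample-size matter and has nothing to do with covariates.

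**4. Simulate under no treatment effect** (3,000 trials each; moderate, fairly strong, strong).

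- No covariates: type I error 4.5, 4.6, 4.1%. Mean model-based standard error against the actual spread of the estimates: 0.1194 vs 0.1170, 0.1194 vs 0.1158, 0.1195 vs 0.1150. The standard error is thus about 2 to 4% too large.
- Stratified by site, plus type: 4.9, 4.9, 5.1%.

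Monte Carlo error is √(0.05 × 0.95 / 3000) = 0.4 point, so only the strong case is clearly below 5% on rejection rate alone. The standard errors show the same direction in all three.

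**5. Second simulation with other assumed strengths.** Site SD 0.4 to 0.5, ARDS-type HR 1.2 to 1.35, PaO2/FiO2 ≤100 HR 1.65 to 1.8, age HR 1.28 to 1.42 per decade; 450 trials per scenario. Power is about 84% unadjusted, 85 to 86% with site and type, and 88 to 89% with PaO2/FiO2 and age added. With no site variation and weaker predictors the gain is about 1 point. These powers match a normal approximation to the mean z statistic, which may slightly understate the unadjusted figure.

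**The case against.** The strongest reply is that silence is not exclusion. The article never calls the Cox model unadjusted, and a covariate list is commonly left to the full protocol or analysis plan, neither of which is shown. This stands, and it is why the point is a request to state the model rather than a charge that the strata are left out. Against it, the Statistics section is specific elsewhere: it names gamma and truncated Poisson models, a 1% trigger for multiple imputation and the R version. The sample size also fits a plain two-group comparison. A reader would reasonably take the model as written to be the planned one.

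A reader might infer that the trial gives away power it already paid for through stratification. The documents do not support this. The 762 patients and 90% power are reproduced without any adjustment, and the stratification factors alone are worth about -1 to +1 point.

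A reader might also blame the missing covariates for power near 85%. That shortfall comes from the mismatch between HR 0.66 and 37% vs 27%. Leaving out covariates did not cause it.

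Nor does the point call for a change to the subgroup analysis: the planned chi-square test for homogeneity already examines whether effects differ between subgroups.

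Finally, the unadjusted hazard ratio lying nearer 1 is not in itself an error. Marginal and conditional hazard ratios are different quantities. In the strong scenario the average estimates are 0.677 without covariates and 0.632 with type and severity.

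**Conclusion.** The point holds as a minor but worthwhile improvement. Randomisation is stratified by site and ARDS type, and the stated primary model names neither factor nor any baseline predictor. As written, the analysis is valid and slightly conservative, with simulated type I error of about 4.1 to 4.6% when the factors are prognostic.

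The size depends on what is added. Site and ARDS type alone move power by about -1 to +1 point, close to simulation error, and stratifying on all 70 cells lowered it in three of four scenarios. Baseline severity adds about 3, 5 or 8 points under moderate, fairly strong or strong prognostic effects, and nothing if it is not prognostic.

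The direction is secure. The size is not, because the documents give no prognostic strengths and the block size and stratum proportions were also assumed.

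**What to change.** Before unblinding, state the primary model as a Cox model with fixed effects for treatment, ARDS type, baseline PaO2/FiO2 and age, the last two as continuous variables. Handle site by stratification or a shared frailty, with a rule fixed in advance for pooling small sites. Do not stratify on all of the roughly 70 site-by-type cells.

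Report the unadjusted hazard ratio as a sensitivity analysis. Add a sentence that the adjusted hazard ratio is conditional on the covariates and may differ from the marginal one.

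The cost is a few lines of analysis-plan text and no new data: the strata are recorded at randomisation, and age and PaO2/FiO2 at eligibility. The article says the analysing statisticians are blinded to group, so the model can still be fixed credibly.

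### The truncated Poisson model named for ventilator-free days either gives standard errors about three times too small or drops every patient with zero days, depending on an unstated truncation side

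*Protocol article*

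**What the plan says.** The Outcome section lists "ventilator-free days at day 28" among the secondary clinical outcomes. It does not say how a patient who dies before day 28 is scored.

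The Statistics section estimates the treatment effect on this outcome by a generalized linear model with "a truncated Poisson distribution (ventilator-free days"). It does not say whether truncation is at zero, at 28 or at both, and it mentions no robust variance, overdispersion term or zero-inflation. The same section places all analyses under intention to treat (an added per-protocol parenthesis is a separate matter).

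The Sample size section supplies the only figures that bear on the shape of the outcome. It assumes a "37% mortality rate at ICU 28 days among moderate-severe ARDS patients" in the control group and adds that "we postulated a 10% reduction in ICU 28-day mortality".

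**The concern.** A Poisson model ties the variance to the mean. Ventilator-free days in moderate to severe ARDS do not behave that way: deaths, if scored 0, form a large spike at zero, and survivors spread over much of the range up to 28.

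The two natural readings of the model fail differently. With the zeros kept and truncation at 28, the point estimate is usable but the model's own confidence interval is far too narrow. With zero truncation, the comparison is confined to patients with at least one ventilator-free day, a group selected by an outcome that the trial expects treatment to change.

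If the mortality result were neutral, a spurious difference in ventilator-free days in either direction could carry undue weight.

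**Working it through.** **Mortality inputs.** The article gives no mean, SD or sample size for ventilator-free days, so the only figure to reproduce is the overall sample size. It starts from "Considering a hazard ratio of 0.66, a 90% power, and a two-sided significance level of 0.05". Schoenfeld's formula gives 4(1.96 + 1.2816)²/(ln 0.66)² = 243.4, so 244 events. If the reduction is absolute, mean mortality is (37% + 27%)/2 = 32%, and 244/0.32 = 762.5, which matches the stated 762. A relative 10% reduction would give mean mortality (37% + 33.3%)/2 = 35.15% and 244/0.3515 = 694, which does not match. The plan therefore rests on 37% against 27%.

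**Assumptions not in the article.** Deaths score 0. Survivors take values from 1 to 28 from a beta-binomial distribution (mean about 16-17 days, SD 4.7 to 7.2). Zero shares of 32%, 37%, 45% and 55% were tried; the higher ones allow for survivors still ventilated at day 28.

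**Dispersion.** Let p be the share of zeros, and m and s the mean and SD of the non-zero values. The overall mean is (1−p)m and the variance is (1−p)s² + p(1−p)m², so

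variance/mean = s²/m + p·m.

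With p = 0.37, m = 15.9 and s²/m = 3.21, this is 3.21 + 5.88 = 9.1. Most of it comes from the zeros.

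**Approximate type I error, zeros kept.** With an overall mean near 10, truncation at 28 hardly alters the Poisson, so model-based standard errors are too small by about √(variance/mean). The error rate is approximately 2[1 − Φ(1.96/√(variance/mean))]. For 9.1, √9.1 = 3.02, 1.96/3.02 = 0.65, and the rate is 0.52.

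**Simulation under no effect.** 420 per arm, 1,000 trials per setting, two-sided 5%. Results at 37% zeros:

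| Survivor mean / SD | Overall mean / SD | Variance/mean | Formula | Truncated at 28, model SE | Same, sandwich SE | Zero-truncated, model SE | Rank test |
|---|---|---|---|---|---|---|---|
| 15.9 / 7.1 | 10.0 / 9.5 | 9.1 | 0.52 | 0.53 | 0.04 | 0.27 | 0.04 |
| 16.7 / 6.0 | 10.5 / 9.4 | 8.3 | 0.50 | 0.48 | 0.05 | 0.17 | 0.05 |
| 17.2 / 4.7 | 10.8 / 9.1 | 7.7 | 0.48 | 0.47 | 0.05 | 0.08 | 0.06 |

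For the model truncated at 28 with its own standard errors, the rate was 0.44-0.50 at 32% zeros, 0.51-0.55 at 45% and 0.54-0.56 at 55%. Variance/mean ran from 6.8 to 12.0 over all settings.

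**Lower bound.** With no spread at all among survivors, variance/mean = p·m. At p = 0.37 and m = 16 this is 5.92, giving a rate of 0.42; at m = 10 it is 3.7, giving 0.31.

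**Zero truncation.** At the planned mortality, deaths alone would remove 0.37 × 420 ≈ 155 control patients and 0.27 × 420 ≈ 113 treated patients, leaving about 265 against 307. Survivors alone are still more dispersed than a Poisson (variance/mean about 1.3 to 3.2), so type I error stays at 0.08-0.27 in these runs. Truncating at both ends gives 0.09-0.28.

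**The case against.** The strongest reply is that the article names a distribution and is silent on the standard errors, a detail often left to an analysis plan that is not shown. This stands in part. A reader might infer that the plan as written produces a false positive about half the time. The documents do not support that unconditionally: the figure needs model-based standard errors, and sandwich errors bring the same model back to about 5%. They do not rescue zero truncation, where the patients are already gone.

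A reader might also infer that the plan drops the deaths. The article does not say so. Under intention to treat, truncation at 28 is the more coherent reading, and zero truncation is only one that the wording leaves open.

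Three further inferences fail:

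- Truncation at 28 respects the upper bound of the outcome, so the bound is not the problem. The zeros and the overdispersion are.
- The sentence under which non-normal continuous variables "will be compared using the Kruskal–Wallis analysis of variance" is a general rule for testing, while the Poisson sentence is specific to this outcome and concerns effect estimation. The two can coexist.
- The article sets no ranking of secondary outcomes, so ventilator-free days cannot be called the leading one.

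Finally, the survivor distribution, the share of survivors still ventilated and the score for death are all assumed. That limits the precision of the figures but not their direction, as the lower bound shows.

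**Conclusion.** The concern holds: the stated model does not suit the outcome. Its consequence depends on two things that the article leaves open.

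- **Truncated at 28, model-based errors:** type I error about 45-55%, or about 30-40% even with identical survivors. With sandwich errors, which are not named, it is about 5%.
- **Zero-truncated:** every patient with 0 days is lost, including all deaths if they score 0. That conflicts with intention to treat and conditions on survival. Type I error is still about 8-27%.

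These figures rest on deaths scoring 0 and on assumed survivor distributions; only the 27% and 37% come from the article. This is a should-fix: the outcome is secondary, and the Kaplan-Meier and Cox analysis of 28-day mortality is unaffected.

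**What to change.** Define ventilator-free days with death by day 28 scored 0 or ranked worst. Replace the truncated Poisson with a Wilcoxon rank test, or with a proportional-odds model adjusted for the stratification factors (site, and pulmonary versus extrapulmonary ARDS), in all randomised patients. Report an effect estimate with a 95% confidence interval. The common odds ratio is convenient, since a difference in medians can be uninformative when a third or more of values tie at zero. The rank test held 4-6% in the simulations and is the two-group form of the Kruskal-Wallis test that the section already names.

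If a mean-based model is preferred, keep all zeros and specify robust or bootstrap standard errors.

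The cost is a few sentences, made before treatment groups are unblinded. Standard R functions suffice and no extra data are needed.
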